### Sensitivity analyses

We will conduct sensitivity analyses falling under three broad categories: (1) Modified study population inclusion and exclusion criteria to evaluate the validity of our IV assumptions in subgroups where there is arguably less equipoise in the choice of second-line treatment^44^; (2) Comparing the larger primary care unlinked cohort with the primary care population linked to secondary care data (HES) and (3) Evaluating the robustness of our statistical methods.

Under the first category of sensitivity analyses, we will exclude people with contraindications for SU (eg, liver disease) who are prescribed SGLT2i, as this prescribing may not be due to CCG preference. We will also expand the eGFR exclusion to all those with eGFR <60 mL/min/1.73m^2^ (vs eGFR <30 mL/min/1.73m^2^ in the main analysis). In addition, we will include people who are censored or die during the first 60 days after a prescription for SU, DPP4i or SGLT2i without a prescription for metformin in the same time period to consider the impact of potentially misclassifying these people as switching from metformin monotherapy instead of adding on to metformin monotherapy. Under the second category of sensitivity analyses, we will repeat the analyses for objectives 1 and 2 limited to the HES-linked subpopulation from CPRD who are eligible for the long-term outcomes (objective 3). Third, we will assess the robustness of findings to alternative statistical models for the LIV approach, outcome regressions and alternative approaches to handling missing data.^45^

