**Figure 1 F1:**
[figure not shown]
Flow diagram illustrating the identification of the study cohort of people with type 2 diabetes mellitus (T2DM) who initiate second-line antidiabetic treatment with metformin and one of sulfonylurea (SU), dipeptidyl peptidase four inhibitor (DPP4i) or sodium-glucose cotransporter two inhibitors (SGLT2i). CPRD, Clinical Practice Research Datalink; eGFR, estimated glomerular filtration rate; HES, Hospital Episode Statistics; MTF; metformin.

We will identify people within CPRD with at least one prescription for metformin monotherapy and one other antidiabetic medication in primary care between 1 January 2011 and 31 March 2020, registered at a general practice (GP) contributing research-quality data at the prescription date, and registered with their GP for at least 1 year prior to the first metformin or other antidiabetic prescription, to ensure that we are studying new users. The study population will be limited to people with a T2DM primary care code, on or before the antidiabetic index date to exclude those prescribed antidiabetic medications for other indications (eg, polycystic ovarian syndrome or pre-diabetes). Using the individual’s entire prescribing history with their registered GP, we will include only people who initiate antidiabetic treatment with metformin, and intensify metformin-monotherapy with a first-time prescription for one of the three second-line antidiabetic drug treatments of interest after 1 January 2014. We chose this date for the evaluation of these three treatments as prior to this only a small minority of people in the UK were prescribed SGLT2i.^4^ People who intensify with two or more drug classes on the same date, who discontinue metformin monotherapy prior to a prescription for SU, DPP4i or SGLT2i, or who are prescribed a different drug class as second-line treatment (eg, thiazolidinedione (TZD), insulin, GLP1RA) will be excluded. In addition, we will exclude people with estimated glomerular filtration rate (eGFR) below 30 mL/min/1.73m^2^ since SGLT2i are contraindicated for this group.^23^ We will also exclude women who were pregnant in the 12 months prior to second-line treatment initiation since prescribing guidelines recommend different treatments for pregnant and breastfeeding women.^24^

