### Strength and limitations

This study will exploit the natural variation in prescribing patterns for second-line antidiabetic treatment across CCGs within similar groups of people by using an IV study design. This design minimises potential biases resulting from unmeasured confounders, a major limitation in observational research. The large and representative sample from UK primary care will improve the generalisability of this study’s results and allow for stratification on prespecified baseline risk factors, helping patients and their providers choose treatments based on personal risk profiles to maximise clinical benefit. While the IV relies on three major assumptions which may limit the validity of our estimates, we will evaluate the strength of our assumptions in sensitivity analyses.

A potential limitation is that the required natural variation in prescribing may not exist for those people who are prescribed SGLT2i as second-line treatment because they do not tolerate or have a contraindication for SU, as per current^6^ NICE guidelines.^3^ We will investigate this potential source of bias by undertaking a sensitivity analysis excluding those in the SGLT2i exposure group with contraindications for SU. In addition, our study may be susceptible to non-differential outcome misclassification, as we are unable to link our data to additional audit datasets with more detailed outcome information (eg, laboratory tests) such as the Myocardial Ischaemia National Audit Project (MINAP).^46^ However, a previous study shows that the majority of MINAP acute MI events in the general England and Wales populations are also recorded in CPRD and HES.^47^

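### The SU-contraindication sensitivity analysis excludes on treatment received, so it leaves the missing variation in place and can tie contraindication to the instrument

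*Protocol article*

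**What the plan says.** Under Sensitivity analyses, the first category is meant to "evaluate the validity of our IV assumptions in subgroups where there is arguably less equipoise in the choice of second-line treatment". Its first item reads: "we will exclude people with contraindications for SU (eg, liver disease) who are prescribed SGLT2i". The reason given is that CCG preference might not be what led to this prescribing. Strength and limitations gives the motive, namely that "the required natural variation in prescribing may not exist for those people who are prescribed SGLT2i as second-line treatment" because of intolerance of or contraindication to SU, and restates the remedy as "undertaking a sensitivity analysis excluding those in the SGLT2i exposure group with contraindications for SU". The two sections agree, so this is not a slip in one place.

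The protocol's other clinical exclusions do not depend on the drug received. In the study population section, "we will exclude people with estimated glomerular filtration rate (eGFR) below 30 mL/min/1.73m^2^ since SGLT2i are contraindicated for this group", and this covers all three groups. The item that follows the disputed one is also general: "We will also expand the eGFR exclusion to all those with eGFR <60 mL/min/1.73m^2".

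**The concern.** An IV analysis can be restricted safely on characteristics fixed before treatment. Restricting on the treatment received is different, because the instrument acts on that variable. Two consequences follow.

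- **The target problem remains.** The worry is that contraindicated people do not show natural variation between the drugs. The rule removes those who received SGLT2i and keeps those who received something else. Planned analyses then predicts every retained person's outcome under each drug and averages the person-level differences. Retained contraindicated people enter those averages although no contraindicated SGLT2i recipient is left to inform the prediction.
- **Instrument independence can be lost.** If high-SGLT2i CCGs give SGLT2i to more of their contraindicated patients, they lose more of them to the exclusion. Contraindication is then associated with CCG prescribing history, contrary to the second condition under IV assumptions. Liver disease, the protocol's own example, is not in the main confounder list under Covariates, so the planned adjustment does not evidently deal with it.

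This is the only check that Strength and limitations names for this limitation. A change from the main result could be an artefact of the rule, and agreement would be hard to read as reassurance.

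**Working it through.** The plan attaches no figure to this analysis, so there is none to reproduce. The yardstick is the smaller clinically meaningful difference under Power considerations, 0.3 HbA1c points.

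**Inputs.** From the document: the exclusion rule, and the 2014 range of the SGLT2i instrument Z across CCGs, 0% to 35%. Assumed, because the document gives none: prevalence of SU contraindication π (2%, 5%, 10%); the probability p that a contraindicated person receives SGLT2i at a given Z; and the outcome difference g in contraindicated people (0.3 to 1.0 HbA1c points worse).

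**Step 1: variation among those retained.** The rule removes everyone who is both contraindicated and on SGLT2i. SGLT2i use among the retained contraindicated people is 0%, whatever π, p or Z.

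**Step 2: balance across the instrument.** The share of retained people who are contraindicated is π(1 − p)/(1 − πp).

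- π = 5%, p = 10%: 0.05 × 0.9/0.995 = 4.5%; p = 60%: 0.05 × 0.4/0.97 = 2.1%.
- π = 10%, p = 10%: 0.10 × 0.9/0.99 = 9.1%; p = 60%: 0.10 × 0.4/0.94 = 4.3%.
- p the same at every Z: no gap. With no exclusion there is also no gap, and with everyone contraindicated excluded the share is 0% throughout.

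**Step 3: effect on a simple IV (Wald) estimate.** Let p = p0 + sZ, where s measures how strongly CCG preference moves SGLT2i use in contraindicated people, and let non-contraindicated people receive SGLT2i with probability Z. After the exclusion, the contraindicated share at Z differs from that at Z = 0 by −πs/(1 − πp0) times the SGLT2i share at Z, which is (1 − π)Z/(1 − πp). The shift in the estimate is therefore −gπs/(1 − πp0). The table takes p0 = 0.20. The last column is a simulation of 2,000,000 people per scenario with a true effect of −0.3 and an unmeasured confounder; it gives the stated exclusion minus exclusion of all contraindicated people.

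| π | s | Shift by formula, g = 0.3 / 0.5 / 1.0 | Simulated, g = 0.5 / 1.0 |
|---|---|---|---|
| 2% | 1.0 | −0.006 / −0.010 / −0.020 | −0.01 / −0.02 |
| 2% | 1.5 | −0.009 / −0.015 / −0.030 | −0.01 / −0.03 |
| 5% | 1.0 | −0.015 / −0.025 / −0.051 | −0.03 / −0.05 |
| 5% | 1.5 | −0.023 / −0.038 / −0.076 | −0.04 / −0.08 |
| 10% | 1.0 | −0.031 / −0.051 / −0.102 | −0.05 / −0.10 |
| 10% | 1.5 | −0.046 / −0.077 / −0.153 | −0.08 / −0.16 |

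With s = 0 the formula gives exactly 0; the simulation (run with p = 0.40 throughout) gave −0.004 to +0.004, which is sampling noise. With s = 0.25, π = 10% and g = 1.0 the shift is 0.10 × 0.25/0.98 = −0.026. If contraindicated people do better by 0.3 points (g = −0.3) and s = 1, it is +0.015 at π = 5% and +0.031 at π = 10%.

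**Step 4: the alternative rule.** Excluding all contraindicated people tracked the full-cohort estimate in the simulation, for example −0.277 against −0.284 at π = 10%, s = 1.5, g = 1.0, where the stated rule gave −0.440.

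**The case against.** The strongest reply is that the motivating scenario is one in which CCG preference does not drive SGLT2i use in contraindicated people. Then s = 0 and the exclusion does not bias the IV estimate. This stands, and the bias must be stated conditionally. It does not settle the matter: the protocol raises that scenario only as a possibility, and partial dependence is plausible, for instance through the choice between SGLT2i and DPP4i. Step 1 also holds when s = 0.

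A reader might infer that the rule favours SGLT2i by construction. The document does not support this: the sign depends on whether contraindicated people do worse or better, and no prognosis is given. A reader might also say that the rule creates the very imbalance it was meant to remove. The stated purpose is to deal with missing natural variation, not with an imbalance.

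Nor does it carry the argument that the SGLT2i group is cleared of contraindicated people while its comparators are not. IV identification needs balance across the instrument, not between treatment groups.

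Finally, every size above is assumed, the largest values need the most extreme combination, and the calculation is a simple Wald estimate without the planned covariate adjustment or the local IV method. All of this stands.

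**Conclusion.** The point holds in limited form. The exclusion conditions on treatment received, in both places where it is described and unlike the protocol's eGFR exclusions. It leaves contraindicated people in the analysis with no SGLT2i use among them, so it does not resolve the lack of natural variation. It biases the IV estimate only if CCG preference affects SGLT2i use in that group.

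Under the assumed prevalence of 2% to 10% and worse outcomes of 0.3 to 1.0 points, the shift is between about 0 and −0.16 HbA1c points. The extreme is roughly half of the 0.3-point benchmark (0.16/0.3 = 0.53), and the direction reverses if prognosis does. No size has been worked out for mortality, admissions or complications. It would be wrong to infer a fault in the main estimates: one sensitivity analysis is affected and the primary analysis is not.

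**What to change.** Define the exclusion by SU contraindication recorded before baseline, alone, and apply it to the SU, DPP4i and SGLT2i groups alike. Replace the wording under Sensitivity analyses, and the restatement under Strength and limitations ("excluding those in the SGLT2i exposure group with contraindications for SU"), with the same sentence. This changes only who enters one sensitivity analysis and implies nothing about which drug anyone should receive. The cost is one phrase in two places and slightly fewer people in that analysis.

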## Introduction

Around 3.5 million people in the UK have been diagnosed with type 2 diabetes mellitus (T2DM) accounting for ~10% of National Health Service (NHS) expenditure.^1^ This proportion is predicted to rise to ~17% by 2035–2036.^2^ T2DM is a progressive disease which requires careful management of blood glucose and diabetes-associated complications.^1^ The National Institute for Health and Care Excellence (NICE) recommends metformin as the first-line antidiabetic treatment in people with T2DM.^1^ In many cases, people with T2DM need further treatment in addition to metformin monotherapy to maintain sufficient glycaemic control.

NICE guidance recommends several drug classes as add-ons to metformin for first-stage intensification, hereafter referred to as second-line treatment. These include sulfonylureas (SU), pioglitazone, dipeptidyl peptidase-4 inhibitors (DPP4i) or sodium-glucose co-transporter-2 inhibitors (SGLT2i).^1 3^ NICE guidance recommends considering individual clinical circumstances when selecting T2DM drug treatment. For instance, SGLT2i are recommended as second-line treatment if the person is at high risk of hypoglycaemia or when SU are not tolerated or are contraindicated.^1 3^ However, these guidelines do not specify a single preferred drug class, either overall or within specific groups sharing clinical characteristics.^1^ Research using a representative sample of the UK primary care population up to 2017 showed that SU, DPP4i and SGLT2i, each in combination with metformin, are the most commonly prescribed second-line treatments.^4^

There is wide variation in the proportion of people prescribed these drugs in addition to metformin across NHS Clinical Commissioning Groups (CCGs), who commission local NHS services, suggesting clinician preference may influence treatment choice.^4^ In particular, the variation in SGLT2i prescribing suggests that some clinicians may prescribe these drugs even for those patients who are not considered at high risk of hypoglycaemia and therefore eligible for SU.

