### Covariates

We will use primary care demographic data, diagnosis codes (Read or SNOMED for CPRD Gold and Aurum, respectively), and laboratory test results recorded prior to second-line treatment initiation, to define our main list of potential confounders. These include age, sex, IMD, time on first-line antidiabetic treatment (as a proxy for diabetes duration), GP size, relevant coprescriptions prescribed within 60 days of second-line treatment initiation (renin-angiotensin system inhibitors, statins), history of proteinuria and comorbidities at baseline (myocardial infarction (MI), unstable angina, stroke, ischaemic heart disease, hypoglycaemia, congestive heart failure (CHF), chronic kidney disease (CKD), end-stage renal disease (ESRD), cancer (any), advanced eye disease and lower extremity amputation). CKD status will be defined using serum creatinine test results to derive eGFR, using cut-points defined by the Kidney Disease Improving Global Outcomes guidelines for CKD, but without requiring two measures 3 months apart.^26^ We will also identify HbA1c, systolic blood pressure (SBP), diastolic blood pressure (DBP), eGFR, body weight and body mass index (BMI)^27^ using values recorded in the 180 days period before the second-line antidiabetic treatment initiation date in the primary care record. Time between baseline clinical measures and second-line treatment initiation will also be included as covariates. We will follow previous observational research,^28^ in undertaking secondary analyses that include additional potential confounders that are defined in primary care records, but for which we anticipate relatively high levels of missing data, namely: ethnicity, high-density lipoprotein (HDL), low-density lipoprotein (LDL), total cholesterol, triglycerides, smoking and alcohol status. In the HES-linked cohort, we will use International Classification of Diseases 10th Revision (ICD-10) diagnosis codes recorded as part of previous hospitalisations in conjunction with primary care data to define comorbidities. We will also use ethnicity recorded in HES for people whose ethnicity is missing within the primary care data. Codelists for all covariates defined in primary and secondary care will be published alongside study results.

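### The check on guideline-directed SGLT2i prescribing removes only people with SU contraindications, although the protocol also names high hypoglycaemia risk and SU intolerance as guideline routes to SGLT2i

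*Protocol article*

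**What the plan says.** All references are to the protocol article.

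- **Introduction.** On the guidance: "SGLT2i are recommended as second-line treatment if the person is at high risk of hypoglycaemia or when SU are not tolerated or are contraindicated". The same section goes on to say that variation in SGLT2i use suggests some clinicians prescribe it "even for those patients who are not considered at high risk of hypoglycaemia and therefore eligible for SU". Absence of high hypoglycaemia risk is thus tied to eligibility for SU.
- **Sensitivity analyses.** The first category is meant "to evaluate the validity of our IV assumptions in subgroups where there is arguably less equipoise in the choice of second-line treatment". Its first item reads: "we will exclude people with contraindications for SU (eg, liver disease) who are prescribed SGLT2i", on the ground that the choice of drug in these people may not reflect the CCG's preference. The category also has a wider eGFR exclusion (below 60 instead of below 30) and an item that adds back people who die or are censored within 60 days without a metformin prescription.
- **Strength and limitations.** Natural variation may be lacking for people given SGLT2i because "they do not tolerate or have a contraindication for SU". The remedy named there is again the exclusion of SGLT2i users with SU contraindications.
- **Covariates.** Hypoglycaemia is among the baseline comorbidities in the main confounder list ("ischaemic heart disease, hypoglycaemia, congestive heart failure (CHF"), so it is adjusted for. It is neither an exclusion nor one of the named subgroups under Planned analyses.

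**The concern.** The instrument is the CCG's prescribing history. It is informative only where the choice of drug can respond to local preference. The protocol recognises that guideline-directed SGLT2i prescribing may break this link, calls it a potential source of bias, and offers one sensitivity analysis to investigate it.

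That analysis is narrower than the protocol's own account of the problem. High hypoglycaemia risk is the first guideline route named in the Introduction. It is absent from the limitation and from the exclusion. SU intolerance is named in the limitation but is also absent from the exclusion. If the main and sensitivity results agree, a reader may conclude that guideline-directed prescribing does not matter, although two of the three routes were not examined. Hypoglycaemia is also a study outcome, so a group selected on hypoglycaemia risk is relevant to it.

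**Working it through.** **1. The sections side by side**

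| Guideline route to SGLT2i | Introduction | Strength and limitations: acknowledged | Exclusion (Sensitivity analyses; Strength and limitations) |
|---|---|---|---|
| High hypoglycaemia risk | yes | no | no |
| SU not tolerated | yes | yes | no |
| SU contraindicated | yes | yes | yes, SGLT2i users only |

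Three routes become two and then one. The eGFR exclusion and the 60-day item in the same category are not defined by hypoglycaemia risk or SU intolerance, so they do not fill the gap.

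**2. Possible size of the hypoglycaemia-risk group**

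Inputs from Power considerations: 6700 SGLT2i users out of 25 700, so 6700/25 700 = 26.1%, taken as 0.26. Assumptions, because the document gives no figure: a share h = 2%, 5% or 10% of the cohort at high risk, and 60% of them on SGLT2i.

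Share of the SGLT2i group that is at high risk = h × 0.60/0.26:
- h = 0.02: 4.6%
- h = 0.05: 11.5%
- h = 0.10: 23.1%

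Not all of these people are on SGLT2i because of guidance; at the overall rate 26% of them would receive it anyway. The excess is the relevant quantity, h × (0.60 − 0.26)/0.26:
- h = 0.02: 0.02 × 0.34/0.26 = 2.6%
- h = 0.05: 0.05 × 0.34/0.26 = 6.5%
- h = 0.10: 0.10 × 0.34/0.26 = 13.1%

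**3. Does sample size stand in the way of a wider exclusion?**

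Reproducing Table 1 first. Inputs: SD 2.4, 80% power, two-sided alpha 0.05/3 (Bonferroni for three pairwise comparisons), and effect multiplied by compliance. The SU:SGLT2i ratio of 7:3 is inferred from the table. For 0.3 points at 70% compliance the diluted effect is 0.3 × 0.7 = 0.21, and

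N(SU) = (2.394 + 0.842)² × 2.4² × (1 + 7/3)/0.21² ≈ 4558, and N(SGLT2i) = 4558 × 3/7 ≈ 1953.

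Table 1 gives 4556 and 1952. All 18 cells reproduce within 2 patients.

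Nominal power at 0.3 points and 70% compliance, the weakest scenario in the table, is Φ(0.21/(2.4 × √(1/n₁ + 1/n₂)) − 2.394). The starting numbers are SU 6000 and SGLT2i 6700, and the share removed is assumed:

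| Share removed | From SGLT2i only | From both groups |
|---|---|---|
| 0% | 0.994 | 0.994 |
| 5% | 0.993 | 0.992 |
| 10% | 0.992 | 0.989 |
| 20% | 0.988 | 0.978 |
| 30% | 0.982 | 0.958 |
| 50% | 0.952 | 0.861 |

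On the protocol's own formula, a wider exclusion is affordable over this whole range for the primary HbA1c outcome. The check says nothing about the rarer long-term outcomes.

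**The case against.** **The contraindication list is open.** The example of liver disease is only an example, codes are normally left to the full plan, and the Introduction's link between hypoglycaemia risk and SU eligibility might let high risk count as a contraindication. This stands as an ambiguity. But the Introduction lists high risk, intolerance and contraindication as separate alternatives, so the wording does not clearly bring the group in.

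**Hypoglycaemia is already adjusted for.** This stands for recorded hypoglycaemia, which enters the models as an observed characteristic, and it limits the consequence for the primary analysis. Adjustment does not test whether the instrument works in that group, which is the stated purpose of this category. Unrecorded risk is neither adjusted for nor removable by a coded exclusion.

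**Variation may well exist in this group.** A reader might infer that people at high hypoglycaemia risk have no prescribing variation at all. The document does not support that. The Introduction lists DPP4i among the add-on options and says that guidance sets no single preferred class, even within groups sharing clinical characteristics. The 60% assumed above itself leaves 40% on another drug. High risk is also a matter of degree, so treating it differently from a contraindication could be defended if the protocol said so.

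**The category is wider than one exclusion.** Correct: it also contains the eGFR and 60-day items. The gap concerns only the item aimed at guideline-directed SGLT2i prescribing. IV assumptions adds a general commitment to reassess each assumption in the full data, but does not name these groups.

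**Conclusion.** The mismatch holds on the text. The exclusion meant to address guideline-directed SGLT2i prescribing covers one of the three routes that the protocol names, and the limitation it answers acknowledges two. Agreement between the main and the sensitivity result would be partial reassurance only.

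This is a minor point about a robustness check. A reader might infer that the primary IV estimate is invalid. The document does not support that: recorded hypoglycaemia is in the main confounder list, and no bias in any estimate has been shown.

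The size is unknown. The excess of about 2.6%, 6.5% or 13.1% of the SGLT2i group rests wholly on the assumed prevalence (2%, 5%, 10%) and the assumed 60% uptake; only the 26% comes from the document. A reader might take the total shares of 4.6%, 11.5% and 23.1% as the guideline-directed part, but these include people who would receive SGLT2i at the overall rate anyway. If only coded hypoglycaemia is used, the group may lie at the low end.

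**What to change.** 1. Reconcile Introduction, Sensitivity analyses and Strength and limitations on which guideline-directed groups the check addresses, and state whether contraindications for SU include high hypoglycaemia risk.
2. Add to this sensitivity analysis an exclusion defined by baseline characteristics, not by the drug received, and applied in all three drug groups. It should remove people with recorded baseline hypoglycaemia, people with SU contraindications and, if identifiable, people with recorded SU intolerance. Fix the definitions before effect estimates are seen.
3. Report the number removed per drug, and state that coded hypoglycaemia captures only part of the risk group.

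This concerns the analysis population only and implies no view on who should receive which drug. The cost is one re-run. Baseline hypoglycaemia is already extracted as a covariate, while SU intolerance may need an extra codelist. The downside is a slightly smaller sample in this sensitivity analysis, which the power check shows is tolerable for HbA1c.
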